#### Intervention efficacy among subgroups

We will use *t*-tests and Wilcoxon rank-sum tests to compare mean quality and patient experience scores of pediatric practices between intervention and control arms among subgroups of women defined by age, race/ethnicity, literacy, and other baseline characteristics, both overall and stratified by parity. We will then use analysis of variance models to evaluate quality and experience scores as functions of intervention status and patient baseline characteristics. Effect modification will be evaluated by means of interaction of the intervention with selected patient baseline characteristics. Results of these models will give insight into characteristics of those mothers for whom the patient navigator intervention proved more valuable.

#### Importance of factors in choosing a pediatrician

We will evaluate the distribution of responses to the five-point scale (‘Did not matter at all’ to ‘Mattered a lot’) for each factor in choosing a pediatrician at baseline and follow up. We will compute a within-subject change in importance for each factor, using t-tests and sign tests to determine whether there is a change from baseline and follow up. Initial analyses will be stratified by parity.

#### Impact of intervention on patient and parent activation to self-manage health care

We will evaluate differences in patient and parental activation change between control and intervention by means of *t*-tests or Wilcoxon rank-sum tests. Analysis of variance models will be used to evaluate change in activation, adjusting for baseline activation levels as well as other patient. Initial models will include an interaction effect for intervention with parity. Results from these models will provide information on the impact of the intervention on changing patient and parental health attitudes, whether or not there was an impact on the quality scores of practices selected.

### Power/sample size

Power was evaluated to detect a difference between intervention groups in mean quality and patient experience ratings of pediatric practices, within strata defined by parity (0, 1+). In an 18-month period, we anticipate 2,250 pregnant women will be seen at the Wesson Women’s OB and Midwifery Clinic. Based upon prior experience with research recruitment in these clinics, we expect to be able to approach about two thirds, or approximately 1,500 women. Of these we anticipate 1,200 will meet age and language eligibility requirements and that 730 will agree to participate, with 650 completing baseline and post-delivery data collection.

Expecting approximately 40% nulliparous women [28], we will need to have at least 130 women in each study arm within strata defined by parity. Quality data were identified on the MHQP website for 18 practices within a 25-mile radius of Springfield, with a mean (SD) quality score of 3.1 (0.5) on nine pediatric measures. Mean (SD) patient experience scores were similar at 3.0 (0.6). Using a significance level of 0.01, we will have power greater than 80% to detect a mean difference of 0.2 units in quality scores between control and intervention, within each stratum of parity. Power is greater than 80% to detect a 0.25 difference in mean patient experience ratings. The magnitude of the differences (0.2, 0.25) would indicate a meaningful difference in mean quality or patient experience rating of practices selected, yet this difference is large enough that we expect it could be detected.

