### Analysis

#### Intervention efficacy

Descriptive statistics will be used to characterize the study population and evaluate the distributions of outcomes, predictors and covariates. We will use *t*-tests and Wilcoxon rank-sum tests to compare mean quality and patient experience scores of the pediatric practices selected between women randomized to the navigator intervention and the information pamphlet control. This analysis will be both overall and within strata defined by parity (0, 1+). Our primary analysis will be intent-to-treat, based upon randomization, whether or not the intervention sessions occurred. Patients who choose practices that do not appear on the MHQP website will not be included in the primary outcome analysis but will be included in secondary outcome analyses. Secondary analysis will adjust for compliance with the intervention. We will also evaluate analysis of variance models for the mean quality and patient experience scores, adjusting for parity and any baseline patient characteristics that were not balanced between the intervention groups. An interaction effect for intervention with parity will be included to test for difference in the intervention efficacy between women selecting a pediatrician for the first time versus those with children. Confounding by covariates will be assessed. In addition we will explore the impact of clustering of women within neighborhoods defined by residential zip code, since location of practice relative to home may have a large impact on choice of practice. Final models will provide an estimate of the patient navigator effect on the quality and patient experience ratings of selected pediatric practice, both overall and by parity, adjusting for important maternal characteristics. If practice scores on the website should change during the course of the study, the scores present during the prenatal period will be used in the analysis.

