This study has limitations. First, women who already have children may be less likely to change pediatricians, even if quality scores for the current pediatrician are low. We have attempted to account for this by stratifying randomization to multiparous and nulliparous women and by asking mothers to rate the level of importance of a range of factors that may impact choice of pediatrician. Second, because the website is only available in English, we are not enrolling patients who are not comfortable with the English language. Few organizations have the resources to make websites available in multiple languages, but this continues to limit access to these data. Third, there is debate about how meaningful these types of quality measures are, with questions about the quality of the data used to develop them and the paucity of data linking them to improved patient outcomes. However, the MHQP website has been recognized for the soundness of the MHQP methods of compiling the performance scores, and there is growing use of these measures for assessment of care quality. Fourth, although we do not include a cost analysis for this intervention, it is possible that it may be prohibitively expensive to undertake outside of the study setting. If the intervention is successful, we plan to explore mechanisms of delivering the intervention in an affordable manner, such as using existing staff in obstetricians’ offices. Additionally, while the study was designed with power to detect differences within strata defined by parity, we may be underpowered to detect differences in secondary outcomes, or within subgroups of patients defined by literacy or ethnicity. It may be possible that as websites improve and become more usable for patients with limited health literacy, the need for a navigator may become less important.

In this paper, we have given a brief description of the rationale for a patient navigator intervention to increase access and understanding of publicly reported pediatric quality data for low-income pregnant women. This study will help determine whether removing barriers to use of quality-of-care data impacts women’s choice of pediatrician. If navigators are found to be effective in this study, patient navigator effectiveness in settings with other vulnerable populations may be warranted.

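### The power claimed within each parity stratum depends on an unstated one-sided test: two-sided, nulliparous women give about 74% and 78%, and 130 per arm allows for no unscored practices

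*Protocol article*

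**What the plan says.** The protocol article, Power/sample size, evaluates power within parity strata (0, 1+). It expects 650 women with complete data, about 40% of them nulliparous, and concludes that "we will need to have at least 130 women in each study arm within strata defined by parity". From 18 practices it takes a mean (SD) of 3.1 (0.5) for clinical quality and 3.0 (0.6) for patient experience. For clinical quality it states: "Using a significance level of 0.01, we will have power greater than 80% to detect a mean difference of 0.2 units in quality scores", expressly within each stratum. For the other primary outcome: "Power is greater than 80% to detect a 0.25 difference in mean patient experience ratings". Sidedness is not given.

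Under Analysis, Intervention efficacy, t-tests are named together with "Wilcoxon rank-sum tests to compare mean quality and patient experience scores of the pediatric practices selected", overall and within parity strata. No directional hypothesis is declared. The same section says: "Patients who choose practices that do not appear on the MHQP website will not be included in the primary outcome analysis". The limitations paragraph of the Discussion contains the clause "the study was designed with power to detect differences within strata defined by parity".

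**The concern.** The 130 per arm is exactly the nulliparous share of the completers, so the claim can be checked from the printed inputs. For a conventional two-sided test at 0.01 the result is below 80% for both primary outcomes. In addition, the 130 is used as if every completer contributed a score, which the plan's own exclusion rule does not allow.

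Within-stratum power is the only justification given for the sample size. The article expects women who already have children to be less likely to change practice, so the nulliparous stratum is where an effect is most plausible, and it is also the stratum that falls short. A null result there would be read against more power than the trial has.

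**Working it through.** **Inputs** (Power/sample size): 650 completers; 40% nulliparous; alpha 0.01; difference 0.2 with SD 0.5 (clinical quality); difference 0.25 with SD 0.6 (patient experience). Equal allocation is assumed, as implied by the same minimum in each arm.

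**Stratum sizes.** Nulliparous: 650 x 0.40 / 2 = 130 per arm, which reproduces the article's figure. Parous: 650 x 0.60 / 2 = 195 per arm. Overall: 650 / 2 = 325 per arm.

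**Formula.** Noncentrality = (difference / SD) x sqrt(n / 2). Normal-approximation power = Phi(noncentrality - z), with z = 2.576 two-sided or 2.326 one-sided at 0.01. The noncentral t is the check.

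**Nulliparous stratum, n = 130.**
- Clinical quality: 0.4 x sqrt(65) = 3.225. Two-sided: Phi(3.225 - 2.576) = 74.2% (t: 73.5%). One-sided: 81.6% (t: 81.1%).
- Patient experience: 0.4167 x sqrt(65) = 3.359. Two-sided: Phi(3.359 - 2.576) = 78.3% (t: 77.7%). One-sided: 84.9% (t: 84.5%).

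The stated figure therefore reproduces one-sided and not two-sided. The Wilcoxon test, taking its relative efficiency as 0.955 under normality (an assumption), gives about 72% and 76% two-sided.

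**What 80% would need, two-sided.** 148 and 137 per arm by noncentral t (146 and 135 by normal approximation). Conversely, at 130 per arm the detectable differences are 0.213 and 0.256 by noncentral t (0.212 and 0.254 by normal approximation).

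**Effect of the exclusion.** The article gives no rate for women choosing an unlisted practice. The 10% and 20% below are assumptions. Power by noncentral t (clinical quality / patient experience):

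| Unscored | Scored per arm | Two-sided | One-sided |
|---|---|---|---|
| 0% | 130 | 73.5% / 77.7% | 81.1% / 84.5% |
| 10% (assumed) | 117 | 67.8% / 72.2% | 76.3% / 80.0% |
| 20% (assumed) | 104 | 61.2% / 65.7% | 70.5% / 74.5% |

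One-sided, clinical quality has 80.1% power at 127 scored women per arm and 79.7% at 126. Losing 4 of 130 per arm (3.1%) is thus enough to break that claim too.

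**Rest of the design, two-sided 0.01, noncentral t.** Parous, 195 per arm: 91.3% and 93.6%. Overall, 325 per arm: 99.4% and 99.7%.

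**The case against.** The article never says the test is two-sided, and at one-sided 0.01 both claims reproduce. That stands, so the arithmetic cannot be called wrong outright. But no one-sided test is declared, the planned tests simply compare the arms, and the power section speaks of a difference between groups. If one-sided was meant, the statement omits the condition it depends on.

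The SDs are printed to one decimal. Two-sided at 130 per arm, clinical quality passes 80% at an SD of 0.465 (80.8% by noncentral t) and patient experience at 0.585 (80.2%), and both values would round to the printed ones. This also stands, but it cuts both ways: at 0.55 and 0.65, the upper ends of the rounding ranges, power is 63.2% and 69.3%. A reader can work only from the printed values.

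Counting all 730 enrolled women gives 730 x 0.40 / 2 = 146 per arm, where two-sided power for clinical quality is 80.0% by normal approximation and 79.5% by noncentral t. That conflicts with the stated 130 and with the expected fall to 650.

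A reader might infer three stronger things, which the documents do not support:
- That the trial as a whole is underpowered. The shortfall is confined to nulliparous women.
- That the article presents within-stratum power as a strength. The clause is a concession inside the limitations paragraph.
- That the SD is wrong because it counts each of 18 practices once. No SD across women is given, so neither the direction nor the size of any error can be shown, and this point does not rest on it.

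**Conclusion.** The concern holds in a conditional form. On the printed inputs and a two-sided test, power in nulliparous women is about 74% for clinical quality and 78% for patient experience, roughly 6 and 2 points short of 80%. The stated figure requires an undeclared one-sided test and, for clinical quality, almost no loss to unscored practices. The exclusion can only lower power below the 130-per-arm figures; by how much is unknown, because no rate is given.

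The practical consequence is modest. Detectable differences move from 0.20 to 0.213 and from 0.25 to 0.256 before exclusions, and no endpoint, test or estimand changes. It is worth correcting because the sample size rests on this statement, but it is not a fatal flaw.

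**What to change.** 1. State whether the 0.01 level is one- or two-sided.
2. If two-sided, restate power in nulliparous women as about 74% (0.2) and 78% (0.25), or as 80% power for differences of about 0.21 and 0.26. The parous figures can be given as 91% and 94%.
3. Say that the 130 per arm means women whose chosen practice has a score, and show power under assumed exclusion rates such as 10% and 20%, labelled as assumptions. This applies under a one-sided test as well.
4. Qualify the clause on within-stratum power in the limitations paragraph to match.

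The cost is wording, with a slightly less favourable stated power. No extra patients are needed. Keeping a two-sided claim of 80% for the original differences would instead require 148 and 137 scored nulliparous women per arm.

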## Discussion

In this paper, we describe our rationale and methods for an RCT to test the efficacy of a patient navigator intervention for increasing the impact of publicly reported quality of care data on the choice of a pediatric care provider. The potential impact of this study is great. With more than 73 million children under the age of 18 residing in the US [34], the quality of ambulatory pediatric care can have an enormous impact on population health.

The impact of publicly reported quality data on patients’ choice has been disappointing, due in part to challenges in communicating the information to patients in a meaningful way [14]. Our study takes a novel approach to making the science of public reporting available and understandable to a population known to be at greatest risk for limited capacity to use these data. Two elements of this study design enhance the potential for success: use of patient navigators and engagement of participants while they are receiving prenatal care. Although patient navigators have been used to assist patients in obtaining preventive care and treatment for complex medical conditions [22-24], we are unaware of studies in which they have been used to enhance informed decision-making about choice of providers for a low income population. Navigators have demonstrated the greatest effectiveness among populations with lower socioeconomic status and low health literacy [25-27]; thus, targeting a population with these characteristics may offer the greatest potential for effectiveness of the intervention. Pregnancy is also a time when women may be more engaged in their health and healthcare than at other times [35]. This motivation, coupled with sufficient lead time between knowing they need to select a pediatrician and selecting one, makes this an opportune time to test navigator efficacy.

If successful, this model has important ramifications. Team approaches to care are increasingly used in the ambulatory setting [36]. Although it is unlikely that a single practice can sponsor a dedicated patient navigator, it seems reasonable that case managers and ancillary staff can be trained to provide information about care quality to patients as part of a global effort to engage patients in health care decision-making. Should this efficacy trial favor use of navigators, this may have important implications for design and scope of responsibilities for care team members.

This study has limitations. First, women who already have children may be less likely to change pediatricians, even if quality scores for the current pediatrician are low. We have attempted to account for this by stratifying randomization to multiparous and nulliparous women and by asking mothers to rate the level of importance of a range of factors that may impact choice of pediatrician. Second, because the website is only available in English, we are not enrolling patients who are not comfortable with the English language. Few organizations have the resources to make websites available in multiple languages, but this continues to limit access to these data. Third, there is debate about how meaningful these types of quality measures are, with questions about the quality of the data used to develop them and the paucity of data linking them to improved patient outcomes. However, the MHQP website has been recognized for the soundness of the MHQP methods of compiling the performance scores, and there is growing use of these measures for assessment of care quality. Fourth, although we do not include a cost analysis for this intervention, it is possible that it may be prohibitively expensive to undertake outside of the study setting. If the intervention is successful, we plan to explore mechanisms of delivering the intervention in an affordable manner, such as using existing staff in obstetricians’ offices. Additionally, while the study was designed with power to detect differences within strata defined by parity, we may be underpowered to detect differences in secondary outcomes, or within subgroups of patients defined by literacy or ethnicity. It may be possible that as websites improve and become more usable for patients with limited health literacy, the need for a navigator may become less important.

In this paper, we have given a brief description of the rationale for a patient navigator intervention to increase access and understanding of publicly reported pediatric quality data for low-income pregnant women. This study will help determine whether removing barriers to use of quality-of-care data impacts women’s choice of pediatrician. If navigators are found to be effective in this study, patient navigator effectiveness in settings with other vulnerable populations may be warranted.

## Trial status

Piloting of study materials, intervention, and navigator training are complete and we are actively enrolling patients.

## Abbreviations

BMC: Baystate Medical Center; MHQP: Massachusetts Health Quality Partners; NVS: Newest Vital Sign; PAM: Patient Activation Measure; PI: Principal investigator; P-PAM: Parental Patient Activation Measure; RCT: Randomized controlled trial; TUSM: Tufts University School of Medicine.
